## Methods

### Study design

A longitudinal prospective cohort study will be conducted to identify clinical phenotypes and prognostic factors for outcomes in pain and disability in individuals with hip OA undergoing THA (HIPPROCLIPS, ClinicalTrials.gov Identifier: NCT05265858). Ethical approval was obtained from the medical ethical committee of Hospital East-Limburg and Hasselt University (B3712021000002). Measurements will be performed at five major timepoints: one week before THA (T0), during the first week after THA (T1), and six weeks (T2), three months (T3), 12 months after THA (T4). During the first week after THA, participants will be asked to complete a minor set of questionnaires on the first, the third, the fifth, and the seventh postoperative day. A timeline and schematic overview of the HIPPROCLIPS-trial can be found in Fig. 1. The HIPPROCLIPS-trial is divided in four sub-studies based on cross-sectional and longitudinal analyses, details on the different studies can be found in Table 1.

**Table 1 Tab1:** Overview of the HIPPROCLIPS-trial studies

Study	Objective	Research Questions (RQ)	Phenotyping variables or candidate prognostic factors	Outcome variables	Design and main statistical method
1	To determine the influence of traumatic experiences and mental disorders on the pain processing of individuals with hip OA and shortly after THA	1. To which extent are traumatic experiences and mental disorders associated with preoperative pain processing in individuals with hip OA waiting for THA? 2. To which extent are traumatic experiences and mental disorders associated with pre- and early postoperative pain-related cognitions and emotions in individuals with hip OA undergoing THA?	- Traumatic experiences (T0) - Mental disorders (T0)	Primary: QST (T0) Secondary: Pain-related cognitions and emotions, other pain-related variables (T0, T1)	**Design**: cross-sectional (RQ1) and longitudinal analysis (RQ2) **Main statistical method**: LASSO regression

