### Statistical analysis

Statistics will be performed in R (Version 3.6.3) using RStudio (2022.07.2). According to the different research questions and the type of data available, different statistical methods will be used (see Table 1). A sample size calculation was performed in R based on the third objective to identify pre- and early postoperative prognostic factors for long-term outcomes in pain and disability after THA for hip OA. A sample size of 200 participants will be needed for a prognostic model with 12 independent variables, a power of 80%, an effect size of 0.15, and a drop out of 20%.

For study 1, a LASSO regression (Least Absolute Shrinkage and Selection Operation) analysis will be used to assess the potential relationship between traumatic experiences and mental disorders on pain processing variables (QST) [91]. LASSO regression is a technique that extends the traditional linear regression by incorporating a regularization term that penalizes the size of the regression coefficients. This penalty aids in reducing model complexity and identifying the most essential predictors. When working with high-dimensional data containing numerous predictor variables, LASSO regression is particularly useful. LASSO is superior to traditional linear regression in its ability to prevent overfitting, enhance model interpretability, and reduce estimate variance.

If no suitable model (autocorrelation, residual distribution) can be found, a neural network will be used to answer this research question [92].

In study 2, since all pre-operative phenotyping variables will be included in the model, decision tree learning will be used to select the most relevant variables to include in the model to identify preoperative clinical phenotypes [93]. Decision tree learning is a type of machine learning algorithm that constructs a tree-like model of decisions. An important distinction between decision tree learning and traditional linear regression is that decision trees can deal with both categorical and continuous data, whereas linear regression requires that independent variables be continuous. In addition, decision trees can account for non-linear correlations between variables and interactions among predictors. Moreover, decision trees are easier to interpret than linear regression models. The structure of the decision tree is readily comprehensible, as are the rules for predicting outcomes.

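### Study 1 asks how strongly trauma and mental disorders relate to pain processing, but its LASSO shrinks those same coefficients and its fallback is a neural network

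*Protocol article*

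**What the plan says.** Table 1 (Study design) gives Study 1 two research questions, both about degree of association. RQ1 asks: "To which extent are traumatic experiences and mental disorders associated with preoperative pain processing in individuals with hip OA waiting for THA". RQ2 asks: "To which extent are traumatic experiences and mental disorders associated with pre- and early postoperative pain-related cognitions and emotions". The exposures for both are traumatic experiences and mental disorders at T0. The outcomes are "Primary: QST (T0") and "Secondary: Pain-related cognitions and emotions, other pain-related variables (T0, T1"). The design is "cross-sectional (RQ1) and longitudinal analysis (RQ2"), and LASSO regression is the single main method listed for both questions.

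The Statistical analysis section says that LASSO "analysis will be used to assess the potential relationship between traumatic experiences and mental disorders on pain processing variables (QST"). It explains that the penalty acts on coefficient size and helps to single out the most important predictors, and it recommends the method for data with very many predictors. It then adds: "If no suitable model (autocorrelation, residual distribution) can be found, a neural network will be used to answer this research question".

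During T1, "participants will be asked to complete a minor set of questionnaires on the first, the third, the fifth, and the seventh postoperative day". Table 2 schedules QST at T0, T2, T3 and T4, but not at T1.

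**The concern.** A question about degree of association for exposures chosen in advance needs an effect estimate and its uncertainty for each of them. LASSO is built to select predictors and to predict. It gains lower variance by biasing coefficients toward zero, and here the penalised coefficients are the ones the objective is about. The Background says that the role of trauma and mental disorders in pain processing is unknown in this population. A coefficient set to zero by the penalty could therefore be read as evidence of no association.

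The fallback makes this worse. A poor residual distribution, or correlation between residuals, is a reason to choose another association model. A neural network does not by default give an interpretable effect estimate with an interval.

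RQ2 has up to five assessments per person (T0 and days 1, 3, 5 and 7). The only method named for it is plain LASSO, and the text describes that method only for QST, which is not an RQ2 outcome.

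**Working it through.** **Inputs from the protocol article.** The planned sample is 200. The 20% drop-out allowance leaves 200 × 0.8 = 160, used here as the lower end. Both figures come from the sample size calculation, which was made for objective 3. No figure is given for Study 1, so there is none to reproduce.

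**What the penalty does.** LASSO minimises (1/2n)·‖y − Xb‖² + λ·Σ|b_j|. For uncorrelated standardised predictors the solution is b_LASSO = sign(b_OLS)·max(|b_OLS| − λ, 0), where OLS is ordinary least squares. Each coefficient moves toward zero by λ, and any coefficient with |b_OLS| ≤ λ becomes exactly zero. Nothing in the text sets λ to zero for the exposure terms.

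**Size, set-up A (assumed).** 12 standardised predictors, two with true coefficient 0.20, residual SD 1, 10-fold cross-validation, 150 replicates per row. The first LASSO columns use the λ with minimum cross-validation error. The last column uses the one-standard-error rule.

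| n | correlation | OLS | LASSO, minimum λ | set to zero | set to zero, 1-SE λ |
|---|---|---|---|---|---|
| 200 | 0 | 0.198 | 0.127 | 12.3% | 90.3% |
| 200 | 0.3 | 0.193 | 0.126 | 10.3% | 77.3% |
| 160 | 0 | 0.201 | 0.114 | 23.0% | 90.3% |
| 160 | 0.3 | 0.190 | 0.121 | 12.0% | 83.3% |

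At the minimum λ the shortfall runs from 1 − 0.127/0.20 = 36.5% to 1 − 0.114/0.20 = 43%. At the 1-SE λ the mean estimate is only 0.008 to 0.016.

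**Size, set-up B (assumed).** 15 predictors, n = 160 to 200, minimum λ. A true 0.15 is estimated at about 0.06 to 0.11, a shortfall of 1 − 0.11/0.15 = 27% to 1 − 0.06/0.15 = 60%. It is set to zero in roughly 12% to 48% of runs, depending on correlation and n. OLS is close to unbiased.

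**Overall error (assumed).** n = 200, five exposures correlated at 0.4 with true effects 0.15, 0.15, 0.10, 0.10 and 0, ten null covariates, 100 replicates. Root mean squared error at 0.15 is 0.08 to 0.09 for both methods. At 0.10 it is 0.07 to 0.08 for LASSO and 0.09 for OLS. LASSO's disadvantage is therefore bias, not total error.

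**RQ2, places side by side.** Table 1 calls RQ2 longitudinal and names LASSO. The Statistical analysis section applies LASSO to QST. Table 2 has no QST at T1. The same section mentions repeated measurements explicitly only for Study 4. The article therefore names no method suited to within-person data for RQ2.

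**The case against.** **The exposures may not be few.** The sections on traumatic experiences and mental disorders describe five CTQ dimensions, six TEC areas, 17 MINI-S disorders, a suicidal-risk module and two HADS subscales: 5 + 6 + 17 + 1 + 2 = 31 possible terms, many of them correlated and some probably sparse. An unpenalised model with all of them could be unstable. This stands, and it limits the remedy to total scores or a small fixed set. It does not make penalised coefficients a good answer to a question of degree.

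**Ordinary regression does not detect more.** In the overall-error simulation, OLS was non-significant at 0.05 in 58% to 65% of runs for a true 0.15, while LASSO set it to zero in 10% to 14%. These are different events, since a non-significant estimate still comes with an interval. But the case against LASSO cannot rest on power. The zeroing rates also depend on the set-up.

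**Detail may sit elsewhere.** The article does not rule out bootstrap or post-selection intervals, so the fair statement is that none comes by default.

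**Stronger readings that the document does not support.**
- A reader might infer that the T1 rows will be analysed as independent. With five rows per person and an assumed intraclass correlation of 0.4 to 0.7, that would make standard errors too small by √(1 + 4 × 0.4) = 1.61 to √(1 + 4 × 0.7) = 1.95. No text says the rows are stacked or treated this way, so the factor cannot be charged to the plan.
- A reader might call the autocorrelation check meaningless. It is relevant to RQ2.
- A reader might infer that confounding is ignored because Table 1 lists no confounders. That column lists phenotyping variables and candidate prognostic factors, and the Discussion commits to defining, measuring and adjusting for confounders.
- A reader might say that a neural network gives no association at all. Importance or partial-dependence summaries are possible.

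**Conclusion.** The point holds as a mismatch between question and method. Study 1 asks for degree of association for exposures named in advance, and the stated method penalises those coefficients without exemption. Under the assumed settings a true standardised 0.15 comes out 27% to 60% too small and is lost in roughly 12% to 48% of runs. A true 0.20 comes out about 36% to 43% too small. These sizes depend on the assumed number of predictors, their correlation, n and the rule for choosing λ, none of which the article gives. The direction of the bias does not depend on them. Total error is similar or sometimes lower with LASSO, so the loss is in unbiasedness and in having an interval.

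The neural-network fallback moves further from the question. On RQ2, the supportable statement is that plain LASSO is the only method named for a longitudinal question and is described only for QST. The document does not show that within-person correlation will be ignored.

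**What to change.** 1. **RQ1.** Fix a small set of trauma and mental-disorder terms in advance (total scores or a short list). Fit them unpenalised and report each association with a 95% confidence interval. LASSO may still be used to select additional adjustment covariates.
2. **RQ2.** Name a linear mixed model or GEE over T0 and days 1, 3, 5 and 7, and state the outcomes it covers.
3. **Fallback.** Replace the neural network with a transformation, robust or bootstrap intervals, or quantile regression, so that an association estimate is reported in every case.

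This changes the analysis wording only and needs no new data. The cost is somewhat higher variance than with a penalised model, and the number of exposure terms must be kept small.

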Indeed, maladaptive pain-related cognitions, emotions, and behavioural factors are known contributors to pain and disability in individuals with musculoskeletal pain, and can lead to poor treatment outcomes [22–30]. Preoperative fear-avoidance behaviour is an important prognostic factor for outcomes after knee and hip surgery [31, 32]. Furthermore, increasing evidence suggests that cognitive appraisals such as perceived injustice contribute to pain and disability in individuals with musculoskeletal disorders, including non-traumatic conditions such as OA [33–36]. Additionally, other psychological and social factors can influence the threat appraisal of pain and the ability to cope with stressful life situations. Evidence suggests that self-efficacy and social support may be associated with the development of disability and the ability to cope with pain [37–39]. Childhood trauma is known to be associated with a higher risk of chronic pain in adulthood, including OA-related pain [40, 41]. Furthermore, traumatic experiences can lead to a significant increase in the risk for mood and anxiety disorders [42, 43]. Symptoms of anxiety are highly prevalent among individuals with hip OA [44] and are known to be associated with higher levels of pain and disability in persons with hip OA and after THA [45]. However, the role of traumatic experiences and mental disorders in the pain processing of individuals with hip OA undergoing THA remains unknown. Furthermore, despite their importance in musculoskeletal disorders, no studies have investigated the existence of clinical phenotypes based on the aforementioned biopsychosocial characteristics, and the prognostic role of factors such as perceived injustice and traumatic experiences has not yet been investigated in individuals undergoing THA for hip OA.

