Finally, the heterogeneity in the clinical presentation of individuals with hip OA and in the outcomes after THA may be explained by the pain mechanisms involved [46]. Increasing evidence suggests that central mechanisms play an important role in the pain experience of individuals with hip OA [47]. Widespread hyperalgesia, increased temporal summation of pain, and altered pain modulation through descending inhibitory pain pathways are known indicators of this central involvement [46]. Mechanistic pain profiling using quantitative sensory testing (QST) has already been used to profile individuals with OA based on involved pain mechanisms [48] and is argued to be a promising method to predict the outcomes of pain and disability after total joint arthroplasty [49, 50]. However, the current body of research has not considered both self-reported biopsychosocial variables and mechanistic pain profiling to identify clinical phenotypes in individuals with hip OA undergoing THA.

Therefore, in line with the above identified knowledge gaps, the following objectives were defined: (1) to determine the influence of traumatic experiences and mental disorders on the pain processing of individuals with hip OA and shortly after THA, (2) to identify pre-operative clinical phenotypes in individuals with hip OA and compare their prognosis for outcomes in pain and disability after THA, (3) to identify pre- and early postoperative prognostic factors for long-term outcomes in pain and disability after THA for hip OA, and (4) to identify postoperative clinical phenotypes based on biopsychosocial characteristics at different timepoints up to one year after THA for hip OA, and their pre- and early postoperative prognostic factors.

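### If Study 1 fits trauma and mental disorders in one LASSO, the trauma coefficient omits what runs through mental disorder and is not the overall association of trauma

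*Protocol article*

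**What the plan says.** The first objective (Background, last paragraph) is "to determine the influence of traumatic experiences and mental disorders on the pain processing of individuals with hip OA and shortly after THA". Table 1 (Study design) turns this into research questions. RQ1 asks "To which extent are traumatic experiences and mental disorders associated with preoperative pain processing in individuals with hip OA waiting for THA"; RQ2 asks the same about pain-related cognitions and emotions before and early after surgery. The Study 1 row lists both factors in one cell, "Traumatic experiences (T0) - Mental disorders (T0"), and gives LASSO regression as the main method.

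The Statistical analysis section says that the LASSO "analysis will be used to assess the potential relationship between traumatic experiences and mental disorders on pain processing variables (QST"). It adds that the penalty helps to pick out the predictors that matter most. It describes no model with trauma alone and no mediation analysis.

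The Background states how the two factors are related: "traumatic experiences can lead to a significant increase in the risk for mood and anxiety disorders". It links each to pain. On trauma: "Childhood trauma is known to be associated with a higher risk of chronic pain in adulthood, including OA-related pain". Anxiety symptoms, it says, "are known to be associated with higher levels of pain and disability in persons with hip OA and after THA".

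**The concern.** Objective 1 asks about trauma as a factor in its own right. If trauma raises the risk of mood and anxiety disorders, and these in turn affect pain processing, part of the association of trauma with QST runs through mental disorder. A model that also contains MINI-S and HADS holds that part fixed. The trauma coefficient then answers a narrower question: what trauma adds among people with the same measured mental disorder status.

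Selection sharpens the problem. If the LASSO drops trauma, or leaves it near zero, the result invites the statement that trauma is not associated with pain processing. That could be wrong for half of objective 1. The same applies to RQ2, for which Table 1 names the same factors and method.

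The mental disorder coefficient is not harmed. On the protocol's causal order trauma precedes mental disorder, so adjusting mental disorder for trauma is proper.

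**Working it through.** **Plan's own figure.** There is none to reproduce here. The only computed figure in the article, the sample size of 200, is based on objective 3, and this point does not depend on it.

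**Inputs.** From the documents: the two factors, the LASSO, and the statement that trauma can lead to mood and anxiety disorders. The documents give no path values, so the following standardised values are assumptions:
- *a*: trauma to mental disorder
- *b*: mental disorder to the pain-processing outcome, given trauma
- *c′*: trauma to the outcome, given mental disorder

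**Formulas** (linear model, no interaction, mental disorder fully measured, no unmeasured common cause of mental disorder and outcome):
- overall trauma coefficient, trauma-only model = *c′* + *ab*
- trauma coefficient, joint model = *c′*
- share removed = *ab* / (*c′* + *ab*)

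**Results.**

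| a | b | c′ | Overall | Joint | Share removed |
|---|---|---|---|---|---|
| 0.4 | 0.3 | 0.10 | 0.10 + 0.12 = 0.22 | 0.10 | 0.12/0.22 = 55% |
| 0.3 | 0.2 | 0.10 | 0.10 + 0.06 = 0.16 | 0.10 | 0.06/0.16 = 38% |
| 0.2 | 0.1 | 0.20 | 0.20 + 0.02 = 0.22 | 0.20 | 0.02/0.22 = 9% |
| 0.5 | 0.3 | 0.10 | 0.10 + 0.15 = 0.25 | 0.10 | 0.15/0.25 = 60% |
| 0.4 | 0.3 | 0 | 0.12 | 0 | 100% |
| 0.4 | −0.3 | 0.20 | 0.20 − 0.12 = 0.08 | 0.20 | none; overstated |

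Rows three and four are the extremes over *a* = 0.2 to 0.5, *b* = 0.1 to 0.3 and *c′* = 0.10 to 0.20.

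**Check with an actual LASSO.** Simulation with n = 200, 60 runs per setting, penalty at the cross-validated minimum (5-fold). Mean trauma coefficients:

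| a, b, c′ | Trauma-only OLS | Joint OLS | Joint LASSO | Trauma dropped |
|---|---|---|---|---|
| 0.4, 0.3, 0.10 | 0.231 | 0.102 | 0.100 | 18% |
| 0.3, 0.2, 0.10 | 0.173 | 0.117 | 0.108 | 7% |
| 0.4, 0.3, 0 | 0.108 | −0.010 | 0.000 | 50% |
| 0.4, −0.3, 0.20 | 0.067 | 0.194 | 0.179 | 12% |

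A separate run under the first setting gave a cross-validated-minimum trauma coefficient of 0.095 in the joint model and 0.216 in the trauma-only model. At this penalty the joint LASSO lands close to the joint OLS. The gap from the trauma-only figure therefore comes from conditioning on mental disorder and not from shrinkage, and removing the penalty would not close it.

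**The case against.** **The joint model is inferred.** The Statistical analysis section lists no predictor set for Study 1, whereas for Study 2 it says that all preoperative phenotyping variables enter the model. Table 1 lists the factors of a study, not the terms of an equation, and exact model composition may be left to a fuller document. This stands as a limit. The point applies to the natural reading, and a statement that trauma is also modelled separately would settle it.

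**The research questions ask about association.** A mutually adjusted association is a legitimate quantity. That stands, provided it is labelled as such. It is still not the overall association of trauma, and the objective speaks of influence.

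**Mediation is not stated.** The Background says that trauma can raise the risk of mood and anxiety disorders and that anxiety goes with pain. It calls the role of both factors in pain processing unknown. The MINI-S covers 17 disorders, not only mood and anxiety. The TEC covers a wide range of events and records age at onset, so a mental disorder may precede some of them. There it could be a confounder, and leaving it out could bias the trauma estimate. This stands, and is why the trauma-only model should be added to the joint model and not replace it.

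**Stronger readings to avoid.** A reader might infer that trauma is bound to be understated. That needs direct and indirect paths of the same sign. The Background supports this for pain and disability, but nothing in the document gives it for QST, and opposite signs produce overstatement. A reader might also infer that the LASSO would almost always discard trauma because of the mediator. Under the heavier one-standard-error penalty it mostly does, but so does a LASSO containing trauma alone (mean coefficient 0.005, kept in 8% of runs under the first setting). That is shrinkage, and the article specifies no such penalty.

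**Conclusion.** The point holds on the natural reading of a single joint model. The trauma coefficient would then describe the association not running through measured mental disorder, and taken alone it would not show the overall association of trauma with pain processing or with cognitions and emotions. Under the central assumed paths it shows 0.10 of 0.22. Across the wider same-sign range the loss is 9% to 60% when a direct effect exists, and complete when it does not.

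All of these sizes rest on assumed paths and on mental disorder being fully captured; imperfect measurement by MINI-S and HADS would remove less. The direction is most plausibly understatement, but the documents do not establish it for QST. What they do support is that a null or dropped trauma term in the joint model could not be read as absence of association.

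**What to change.** For RQ1 and RQ2:

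1. State whether the overall association of trauma, the association given mental disorder, or both are wanted.
2. Keep the joint model (CTQ, TEC, MINI-S, HADS). Use it for mental disorder adjusted for trauma, and label its trauma coefficient as the association given measured mental disorder.
3. Add a model with CTQ and TEC but without MINI-S and HADS, reported as the overall association of trauma.
4. Do not conclude from the joint model alone that trauma is unassociated with the outcome.
5. As a check, show a version of the trauma-only model with CTQ only. It covers childhood, so it is less open to a mental disorder having come before the event.

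The cost is one extra model per outcome, plus the optional check, on data already collected at T0. The downside is small: the trauma-only estimate may be confounded where a mental disorder preceded adult events on the TEC, which is why both models should be reported side by side.

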If this approach is not successful, random decision forest will be used [94]. However, it is preferred to keep the model as simple as possible to ease the clinical interpretation.

For the study 3 gradient boosting algorithms will be applied to the dataset to select the best prognostic factors for long-term outcomes in terms of pain and disability [95]. Gradient boosting techniques are a type of ensemble learning that combines numerous weak predictors to create a more accurate one. It adds decision trees to the model in an iterative manner, with each new tree aiming to correct the errors of the preceding trees. Gradient boosting algorithms are especially effective when working with complex data and are frequently capable of achieving high accuracy on a wide variety of problems compared to stepwise linear regression. Previous contralateral THA will be included as a covariate in the analysis to account for possible bias due to knowledge of surgical procedures and postoperative recovery course.

Finally, for study 4, recurrent neural networks (RNN) will be applied to identify postoperative clinical phenotypes based on the multiple data points (repeated measurements during T2, T3, and T4) [96]. RNNs are a sort of neural network architecture that can process sequences of inputs, such as time series. They can keep an internal memory of previous inputs and use it to make predictions about future inputs. RNNs are particularly good for modelling complex temporal interactions. When working with sequential data, RNNs tend to be more flexible and robust than stepwise regression. They are able of modelling complex temporal relationships and less susceptible to overfitting.

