
In addition to the strengths and innovative aspects of this study, there are also some practical issues and potential limitations to consider. In a recent systematic review [101], we investigated contextual prognostic factors for outcomes in the International Classification of Functioning, Disability and Health activity and participation domain after THA in individuals with hip OA. In this review, the main issues in prognostic factor research in individuals after THA for hip OA were discussed. Currently, most studies on prognostic factors for outcomes after THA have a high risk of bias, with mainly problems regarding study attrition and confounding. Therefore, an important practical consideration for this study will be to limit drop-out and accommodate study attrition of participants. The timepoints for follow-up measurements will therefore be scheduled together with the postoperative monitoring appointments with the surgeon to reduce the burden on participants. Furthermore, confounders will be clearly defined and measured using valid and reliable tools, and will be appropriately accounted for in the statistical analysis. One of the limitations of this study will be that generalizability will be limited to individuals with hip OA eligible for THA, and individuals undergoing direct anterior approach THA, since there is a significant preselection of individuals with hip OA undergoing direct anterior approach THA. Furthermore, no external validation is included in this study protocol. When a certain subgroup classification or prognostic factors will be identified, replication of the findings will be necessary in another sample.

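### Study 2 takes phenotypes from a simple decision tree over about 38 variables in 200 people; unless the groups are sharply separated, they are at high risk of changing in a new sample, and the fallback forest supplies no groups.

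*Protocol article*

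**What the plan says.** The Statistical analysis section of the protocol article enters every preoperative phenotyping variable in study 2 and states that "decision tree learning will be used to select the most relevant variables to include in the model to identify preoperative clinical phenotypes". Table 1 lists decision tree learning as the main method, describes the design as cross-sectional on baseline data, and gives HOOS as the primary outcome. The text does not name the variable on which the tree splits.

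The fallback is one sentence: "If this approach is not successful, random decision forest will be used". The sentence after it prefers a simple model so that clinicians can interpret it.

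On size, "A sample size calculation was performed in R based on the third objective", and "A sample size of 200 participants will be needed for a prognostic model with 12 independent variables". That objective is study 3.

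The Discussion acknowledges that "no external validation is included in this study protocol" and that findings will have to be replicated in another sample. It also presents the phenotypes as a possible basis for precision medicine and for enrichment in later randomised trials.

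**The concern.** A classification tree is built greedily. The first split takes whichever variable happens to look best, and every later split depends on it. When many correlated scores carry similar amounts of information, small sampling differences change the first split and with it the whole tree. Study 2 offers many such scores (fear-avoidance, kinesiophobia, injustice, anxiety and depression, trauma, eleven sensory measures) in a sample planned for about a third as many predictors.

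Study 2 asks which phenotypes exist, so the groups themselves are the result. If they depend on the sample, their prognostic comparison in study 2, their link to the postoperative phenotypes in study 4, and any later enrichment trial inherit that dependence. The fallback does not repair this: a random forest averages many different trees and returns predictions and importance rankings, not one partition of patients.

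**Working it through.** **1. The plan's own figure.** The inputs, all from Statistical analysis, are 12 predictors, power 80%, effect size 0.15 and dropout 20%. Alpha and the effect-size metric are not stated; I assume 0.05 and f². For the overall F test with noncentrality λ = f²·N, 80% power needs N = 127, and 127/0.8 = 158.75, so 159 recruited. The stated 200 is not reproduced under these assumptions. It exceeds what they require: 200 × 0.8 = 160 evaluable gives power 0.91. That is a separate matter and does not support this point. What matters here is that the calculation concerns 12 predictors and study 3.

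**2. Number of inputs in study 2** (Table 2 and the section on other pain-related variables, one total per scale):
- sociodemographic and biomedical: 11
- pain-related cognitions and emotions: 3
- self-efficacy, social support, perceived stress: 3
- traumatic experiences: 2
- mental disorders: 3 (4 if HADS enters as two subscales)
- sensory testing: 4 thresholds × 2 sites + 3 = 11
- other pain-related: 5

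The sum is 38 (39 with two HADS subscales), and 38/12 = 3.2 times the number in the sample size calculation.

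**3. Signal strength.** The documents give none for study 2. As a low anchor, f² = 0.15 corresponds to R² = 0.15/1.15 = 0.13. This is borrowed from study 3, so R² up to 0.50 or more was also examined.

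**4. Simulation.** Pairs of independent samples of n = 200 were drawn, a regression tree was fitted to each, and both trees were applied to the same 2,000 subjects. The target is continuous by assumption.

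| Assumed truth | R² | Same first split | Adjusted Rand index |
|---|---|---|---|
| 4 linear predictors among 38, pairwise r = 0.25 | 0.13 | 10% | 0.05–0.06 |
| same | 0.30 | 14–21% | 0.09–0.10 |
| same | 0.50 | 22% | 0.15 |
| 12 linear predictors among 39, correlated blocks | 0.13–0.50 | 3–13% | 0.02–0.10 |
| True four-group threshold structure on 3 variables | 0.13 | 48% | 0.22 |
| same | 0.30 | 95% | 0.53 |
| same | 0.50 | 100% | 0.84 |
| same | 0.70 | 100% | 0.89 |

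Rows 1 to 3 use two levels of splits, at least 20 per leaf and 300 pairs; ranges are from two independently coded runs. The other rows use four-leaf trees, at least 10 per leaf and 60 pairs, so proportions carry a Monte Carlo error of up to about 6 points. A further independent run gave 0.05 to 0.15 for diffuse signal at R² 0.13 to 0.50, and 0.50 and 0.77 for threshold groups at R² 0.30 and 0.50.

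**5. Variable selection alone.** For diffuse signal, the overlap of the split variables between two samples was 0.04 to 0.16 in the block setting and 0.09 to 0.34 in the further run. In the four-predictor setting at R² 0.13, only 41 to 42% of split variables were true predictors.

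**6. Does pruning or a shorter list solve it?** With tree size chosen by 10-fold cross-validation, no split was made in 12 to 69% of diffuse-signal samples, and agreement stayed at 0.00 to 0.14. For threshold groups at R² 0.13, cross-validation raised agreement from 0.22 to 0.51. With nine inputs instead of 38, diffuse R² 0.13 still gave 0.11.

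**7. Can the data show which case applies?** Largely, yes. Agreement between the original tree and a bootstrap refit was 0.20 to 0.30 for diffuse signal and 0.71 for sharp groups. Bootstrap agreement is optimistic because the samples share patients: at R² 0.13 it was 0.20, against 0.06 for truly independent samples.

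**The case against.** The strongest reply is that the result is conditional. A reader might infer that another sample would certainly yield different phenotypes. The documents do not support that: they give neither the strength nor the shape of the signal, and with sharp threshold groups the partition largely reproduces. Whether such groups exist is what study 2 asks. This stands, and it limits the point to a risk. Against it, the article offers no figure that suggests sharp separation. The Background describes multifactorial heterogeneity, reports phenotype classifications in knee osteoarthritis, and calls the evidence in hip osteoarthritis limited.

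Second, the 0.15 belongs to study 3 and the tree's target is unnamed. Both stand. R² = 0.13 is therefore only one end of a range, and the diffuse-signal result does not depend on it.

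Third, the quoted sentence can be read as variable selection feeding a separate phenotype model, rather than leaves serving as phenotypes. That reading is possible and makes the forest a coherent fallback for selection. It does not remove the instability, since the selected variables also change (step 5), and the phenotypes must then come from something other than the forest.

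Fourth, a journal article may leave pruning, cross-validation and internal validation to a fuller plan. Their absence is no error and is not the ground for this point, which rests on what the text does fix: the method, the inputs, the sample, the preference for simplicity and the fallback.

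Fifth, the Discussion asks for replication in another sample. That tempers any claim that later trials would enrich on noise. It does not tell readers of this study which phenotypes deserve replication, which the same data can partly show.

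**Conclusion.** The concern holds as a conditional one. A simple tree over about 38 or 39 variables in 200 people, a size set for a 12-variable model in another study, is at high risk of producing groups that a new sample would not reproduce, unless the phenotypes are sharply separated. Agreement is about 0.05 to 0.15 for diffuse signal at R² 0.13 to 0.50 (somewhat lower in the block setting), against about 0.5 to 0.8 for true threshold groups at R² 0.30 to 0.50. The fallback forest does not by itself answer which phenotypes exist.

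These figures assume a continuous target, one total per scale, small trees of about four leaves and the correlation patterns stated above. They show a range of plausible behaviour and do not predict this dataset.

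One sentence is plainly wrong: the claim that "linear regression requires that independent variables be continuous". Categorical predictors enter a linear model through indicator coding. A reader might take this as undermining the choice of a tree, but the article also cites non-linearity, interactions and ease of interpretation. The error is minor and changes no result.

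**What to change.** - Refit the whole tree procedure, including any tuning, in bootstrap samples (for example 500). Report for each phenotype how often its split variables and its members recur.
- Name a phenotype only if it meets a stability limit set before the data are analysed. Because bootstrap agreement is optimistic (step 7), justify the limit rather than borrow a conventional one.
- State that no stable phenotype is an admissible result of study 2.
- Use the random forest for variable importance only, not as a replacement source of phenotypes.
- Correct the sentence on linear regression.

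Shortening the input list may help but is not sufficient (step 6).

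The cost is analysis wording and computing time; no patient, visit or measurement changes. The real downside is that fewer phenotypes, or none, may be reported.
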